### Strategies to improve adherence to interventions {11c}

Instructions for how to administer medication will be provided to the caregivers by the investigators. Moreover, the patients and their caregivers have access to a 24/7 on-call service, which they can call to make clarifications and to receive medical support when needed.

At each time-point (i.e. daily), the investigators will conduct a home visit to ensure that the medication has been appropriately administered and that the ratings have been recorded.

### Relevant concomitant care permitted or prohibited during the trial {11d}

There are no limitations on other medications, herbs, vitamins, and mineral supplements other than study agents while participating in the study. Additionally, if there were any assistance required after-hours (related to the trial or not), the caregivers will have access to the emergency helpline. The study team will also be notified to render assistance if needed. All medications (prescription and over the counter), vitamin and mineral supplements, and/or herbs taken by the participant will be documented and used to control for confounding factors if needed.

### Provisions for post-trial care {30}

As this trial involves patients whose prognoses are between 3 and 7 days, patient death is expected by the end of the trial. However, in the event the patient outlives the prognoses and survives, the patient’s primary nurse and staff will continue to provide standard palliative care to the patient. At this point, medical advice and end-of-life decisions will be made independently from the study. The patient’s survival (whether alive, discharged, or deceased) will be monitored up to day 7 of recruitment. If the patient is still alive after day 7, their data will be removed from the main analysis as they would no longer fall under the inclusion criteria of an imminently dying patient.

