**Methods:**

Eighty patients with a prognosis of 7 days or less will be recruited for an open-label randomised control trial. The two arms compare oral-transmucosal haloperidol 2.5 mg vs olanzapine 5 mg over 72 h. The severity of agitation, delirium and toxicities of treatments will be compared at the 24th, 48th and 72nd hour after drug administration.

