### Eligibility criteria {10}

The Inclusion criteria for the trial are as follows:
Patient is above 21 years of age.Patient was diagnosed with a terminal illness and is receiving end-of-life care at home.Patient is assessed to be acutely dying (estimated prognosis of 3 days or less).Patient is diagnosed by the primary palliative care provider to have delirium, as described in the DSM-V [6]

The Exclusion criteria are as follows:
Patient does not have a caregiver at home.Patient has a prior history of dementia, psychosis, schizophrenia or any other mental health issue followed up by psychiatrists or other specialists.Patient is currently receiving or has been administered haloperidol or olanzapine less than a week before participating in the study.Patient has known allergies or adverse reactions to haloperidol or olanzapine.

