#### National Cancer Institute Common Terminology Criteria for Adverse Events [17]

Possible side effects of taking either drug include over sedation and extrapyramidal symptoms (akathisia, extrapyramidal disorder, and spasticity). To track these adverse events and their severity, the study team physician will rate observed adverse events using the scale provided by the criteria at 24 h, 48 h and 72 h.

The trial will be conducted for up to 72 h after recruitment; the trial may be stopped earlier in the event of the patient’s death or to ensure the patient’s safety and well-being. If the patient completes the trial and survives, the patient will continue to receive support from their palliative care providers. Patients who survive beyond 7 days after recruitment will be excluded from per-protocol analysis, as they no longer fit the inclusion criteria for the study, i.e. no longer imminently dying.

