### Methods in analysis to handle protocol non-adherence and any statistical methods to handle missing data {20c}

Given the unstable state of the patient, and the community setting being a more difficult-to-control environment, protocol non-adherence may occur due to a variety of real-world factors. The investigators will document instances of non-adherence and assess if the patient would need to be withdrawn from the trial; patient safety and comfort would be prioritised.

To handle protocol non-adherence, analysis will be done on an intention-to-treat analysis basis; participants would be classified according to the treatment they were originally randomised. This analysis method would best reflect the original trial design.

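### Patients alive after day 7 are removed from the main analysis, a selection on survival after randomisation that contradicts the stated intention-to-treat analysis and can bias the comparison

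*Protocol article*

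**What the plan says.** Three places in the protocol article bear on who is analysed.

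- **Provisions for post-trial care {30}.** Survival "will be monitored up to day 7 of recruitment". The rule is then: "If the patient is still alive after day 7, their data will be removed from the main analysis". The reason given is that such a patient no longer meets the inclusion criterion.
- **Plans for assessment and collection of outcomes {18a}, under the NCI-CTCAE subheading.** "Patients who survive beyond 7 days after recruitment will be excluded from per-protocol analysis". The reason is the same, but the analysis named is different.
- **Section {20c}, on non-adherence and missing data.** "analysis will be done on an intention-to-treat analysis basis", which is explained as meaning that "participants would be classified according to the treatment they were originally randomised".

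The inclusion criterion in Eligibility criteria {10} reads: "Patient is assessed to be acutely dying (estimated prognosis of 3 days or less". Outcomes {12} places the MDAS assessments at baseline, 24, 48 and 72 h.

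**The concern.** Survival past day 7 is an event after randomisation. Sedation, toxicity or control of delirium could affect it, and the two drugs may differ in these respects. A main analysis that keeps only patients who died by day 7 therefore selects its population on something treatment may have changed. If that selection differs between arms and is related to MDAS change, the groups compared are no longer those that randomisation formed.

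The trial is open-label and aims to show non-inferiority. With two statements in print about which analysis loses these patients, the main population could be settled after the data are known. Even with no bias, the result would describe only patients who went on to die within the week, a group no clinician can identify when prescribing.

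**Working it through.** **1. The statements side by side.** Section {18a} and section {20c} can both hold: an intention-to-treat main analysis, plus a per-protocol analysis without the day-7 survivors. Section {30} fits neither. It takes randomised, treated patients out of the main analysis, and it applies to the main analysis an exclusion that {18a} confines to the per-protocol one.

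**2. The stated reason.** The criterion in {10} is a clinician's estimate made at entry. A patient who met it at randomisation was eligible. Living longer shows that the estimate was wrong, not that the criterion was unmet.

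**3. Timing.** The last MDAS assessment is at 72 h (day 3). Day-7 status is known 7 − 3 = 4 days later. The rule therefore cannot avoid any data collection; it only discards data already held.

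**4. How many patients might be removed.** The documents give no survival rate. Assume exponential survival, so that P(alive after day 7) = 0.5^(7/median), and apply it to the recruitment target of 80.

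| Assumed median | P(alive after day 7) | Of 80 |
|---|---|---|
| 1.5 days | 0.5^4.67 = 0.04 | 3 |
| 2 days | 0.5^3.5 = 0.09 | 7 |
| 3 days | 0.5^2.33 = 0.20 | 16 |
| 4 days | 0.5^1.75 = 0.30 | 24 |

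Table 3 requires 64 and recruits 80, a margin of 80 − 64 = 16. At a 3-day median the rule alone uses all of it, before any other loss.

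**5. Possible bias.** This is an illustration on assumed inputs. Take the protocol's SD of 7.64 and a latent survival variable with correlation r to MDAS improvement, and drop the longest-surviving share p of an arm. That arm's mean improvement falls by 7.64 × r × h(p), where h(p) = φ(z)/(1 − p), φ is the standard normal density and z is the normal quantile at 1 − p. This gives h(0.05) = 0.109, h(0.10) = 0.195, h(0.20) = 0.350 and h(0.30) = 0.497. With no true difference, the spurious difference is 7.64 × r × [h(larger share) − h(smaller share)].

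| Shares removed | r = 0.3 | r = 0.5 |
|---|---|---|
| 20% v 20% | 0 | 0 |
| 10% v 20% | 0.36 | 0.59 |
| 10% v 30% | 0.69 | 1.15 |
| 5% v 30% | 0.89 | 1.48 |

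These are MDAS points, to be read against the 2-point minimal important difference in Sample size {14}.

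**6. Direction.** Now let the true difference be 2.0 with r = 0.5. If both arms lose the same share, the difference stays 2.0. If the better arm loses 20% and the other 10%, it becomes 2.0 − 0.59 = 1.41. With the shares reversed it becomes 2.0 + 0.59 = 2.59. With r = 0 it stays 2.0 in every case. The gap can therefore shrink, widen or stay the same.

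**The case against.** The rule has a clinical rationale. Trial design {8} defines terminal delirium by closeness to death and says that survivors up to 7 days are included, so removing longer survivors is a pre-specified attempt to match the target condition. The words in {30} might also be a loose label for the per-protocol set named in {18a}, and {20c} introduces intention to treat only as a way to handle non-adherence. Finally, not every day-7 survivor will have full 72 h data, because {11b} ends a patient's contribution at discontinuation.

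The rationale makes the restricted set a fair secondary analysis. It does not justify defining the main population by later survival. If {30} was a slip, it still needs correcting, because it names the main analysis explicitly. The point about incomplete data stands: what is lost is whatever MDAS data were collected, not always a complete series.

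A reader might go further and infer that the survivors are the best responders, so that the rule pulls the arms together and favours a false non-inferiority claim. The documents do not support that. They contain nothing on how survival relates to response, and the Background calls terminal delirium refractory. A narrowed gap requires the better arm to lose more patients and survival to be related to MDAS improvement. Both are assumptions.

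**Conclusion.** The point holds. As written, {30} contradicts {20c} and {18a}, rests on a mistaken reading of the inclusion criterion, and discards primary-outcome data from eligible randomised patients. It should be corrected because it defines the main analysis population.

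The harm is a possibility of unknown size and direction. Bias is near zero if equal shares are removed or if survival is unrelated to MDAS change; otherwise it can go either way. It would be too strong to say that the rule destroys the randomised comparison. The loss of about 7 to 24 of 80 patients rests on exponential survival with medians of 2 to 4 days, and a shorter median would make it smaller.

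Separately, the entry prognosis is not stated consistently. The Abstract has "Eighty patients with a prognosis of 7 days or less will be recruited", {10} sets 3 days or less, {30} speaks of between 3 and 7 days, and {8} includes survivors up to 7 days. This is an eligibility inconsistency and adds nothing to the argument on the analysis set.

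**What to change.** Delete the removal in {30}. State that the main analysis keeps all randomised patients in their assigned arm, with all available MDAS data to 72 h, whatever their survival. Keep the day-7 restriction only as a labelled sensitivity or per-protocol analysis, citing the definition of terminal delirium in {8} as its motive. Align {18a}, {20c} and {30} so that they name the same analysis sets.

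Separately, reconcile the prognosis statements in the Abstract, {8}, {10} and {30}. Which one applies is for the investigators to decide.

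The cost is wording only, with no added visits or data. The small downside is that the main population will include some patients whose prognosis was misjudged at entry, as would also happen in practice.

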### Outcomes {12}

The primary outcome is the reduction in delirium severity as measured with the Memorial Delirium Assessment Scale (MDAS). Secondary outcomes are the reduction in the severity of agitation as measured with the Richmond Agitation-Sedation Scale modified for palliative care (RASS), and the frequency and severity of medication toxicities, as measured using the National Cancer Institute Common Terminology Criteria for Adverse Events (NCI-CTCAE). These data will be collected over four time-points: (i) baseline, (ii) 24 h after commencement, (iii) 48 h after commencement, and (iv) 72 h after commencement.

### Participant timeline {13}

The participant timeline is shown in Fig. 1.

**Fig. 1 Fig1:**
[figure not shown]
Flowchart of clinical trial procedures

### Sample size {14}

Based on validation studies by Breitbart et al. [13] and Lawlor et al. [14], the mean scores from the Memorial Delirium Assessment Scale for patients with delirium is roughly 18 (SD = 7.64). Jain et al. [10] reported that using either haloperidol or olanzapine led to a nearly 55% reduction in patients’ MDAS score (7–8 points). Based on this, we estimate 2 points to be the minimal important difference between haloperidol and olanzapine; a 2-point difference between the treatment arms is equivalent to a 25% difference in the reduction of a patient’s MDAS score. Table 3 details sample size calculations, using the parameters as presented above.

**Table 3 Tab3:** Sample size calculation for repeated measures design

Sample size calculation for repeated measures design	
Standard deviation (drawn from literature review)	7.64
Estimated minimal important difference (effect size)	2
Target power (1-β error probability)	.80
Target *alpha*	.05
Estimated required size per treatment arm	32
Estimated minimum sample size for two arms	64
Target recruitment size (accounting for 30% attrition)	80

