## Statistical methods

### Statistical methods for primary and secondary outcomes {20a}

For the first primary outcome, changes to the severity of delirium over three 24-h periods, as measured with the MDAS, would be analysed using repeated-measures, between-factors ANOVA. If a statistically significant difference is found between medications, post hoc analysis will be conducted to analyse the change in MDAS scores at each time-point.

The second outcome, changes in the patient’s agitation, will be measured using the RASS score. Similarly, the repeated-measures, between-factors ANOVA would be used to analyse the differences in scores.

Additional outcomes of interest are possible toxicity effects due to the medication, which is measured using NCI CTCAE. For each group, the frequency of toxicities (Akathisia, Extrapyramidal disorder, and spasticity) for each group will be compared.

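### Table 3's 32 per arm does not follow from its stated inputs, and the named between-factors test cannot reach 80% power for 2 MDAS points at any non-negative correlation

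*Protocol article*

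**What the plan says.** The Sample size section of the protocol article reports from validation studies that "the mean scores from the Memorial Delirium Assessment Scale for patients with delirium is roughly 18 (SD = 7.64"). This is the spread of raw scores, not of changes. It then says "we estimate 2 points to be the minimal important difference between haloperidol and olanzapine". The article adds that "Table 3 details sample size calculations, using the parameters as presented above".

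Table 3 is titled as a calculation for a repeated measures design. It lists SD 7.64, difference 2, power .80 and alpha .05. From these it gives 32 as the "Estimated required size per treatment arm", 64 as the "Estimated minimum sample size for two arms", and 80 as the "Target recruitment size (accounting for 30% attrition"). It does not state the within-patient correlation, the number of measurements, the sidedness of alpha or the formula.

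The Statistical methods section says that change in MDAS over the three 24-hour periods "would be analysed using repeated-measures, between-factors ANOVA". The Outcomes section places MDAS at baseline, 24, 48 and 72 hours. The Objectives section calls the trial non-inferiority and gives no numerical margin.

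**The concern.** A difference of 2 against an SD of 7.64 is a standardised effect of 2/7.64 = 0.26. Thirty-two per arm is far too few to detect that with 80% power unless the repeated measurements remove most of the variance. A between-factors test cannot do so, because it compares patient averages, and positive correlation between visits makes those averages more variable.

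At stake is the trial's ability to answer its own question. If 2 points is also the non-inferiority margin (an inference, since Objectives gives none), a trial of this size could see no difference at all and still fail to exclude a 2-point deficit. Readers would meanwhile believe it had 80% power to do so.

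**Working it through.** **Inputs.** From Table 3: SD 7.64, difference 2, power .80, alpha .05, 32 per arm, 64 in total, 80 recruited, 30% attrition. From Outcomes: three post-dose visits plus baseline. Allocation is 1:1. Assumed, because not stated: a common correlation r between visits, the same SD at every visit, and both one-sided and two-sided alpha.

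**Attempt to reproduce 32.** With variance factor F, n per arm = 2 × (z_alpha + z_beta)² × 7.64² × F / 2².
- Single comparison (F = 1), two-sided: 2 × (1.960 + 0.842)² × 58.37 / 4 = 229, or about 230 with the t distribution.
- One-sided 0.05: 2 × (1.645 + 0.842)² × 58.37 / 4 = 180, or 182 with t.
- At 32 per arm the standard error is 7.64 × √(2/32) = 1.91. The noncentrality is 2/1.91 = 1.05, and power is 18% two-sided and 27% one-sided.

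The stated inputs alone do not give 32.

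**How small F must be.** For 32 per arm to suffice, F must be about 32/229 = 0.14 two-sided or 32/180 = 0.18 one-sided. With t the limits are slightly lower.

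**The named between-factors test.** For the mean of m visits, F = (1 + (m−1)r)/m. Its smallest value over r ≥ 0 is 1/m: 0.333 for three visits and 0.25 for four. Both exceed the limits above. Power at 32 per arm (noncentral t):

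| Visits averaged | r | F | Two-sided | One-sided |
|---|---|---|---|---|
| 3 | 0 | 0.333 | 43% | 56% |
| 3 | 0.5 | 0.667 | 24% | 35% |
| 4 | 0 | 0.250 | 54% | 67% |
| 4 | 0.5 | 0.625 | 26% | 37% |
| either | near 1 | near 1 | 18% | 27% |

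The four-visit rows are generous. They assume a 2-point difference in the average of all four visits, yet baseline precedes treatment, so a 2-point post-dose difference averages only 2 × 3/4 = 1.5.

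**Analyses that use baseline** (mean of three post-dose visits).
- Baseline-adjusted, F = (1 + 2r)/3 − r²: r = 0.5 gives 0.417 and 36% power two-sided; r = 0.8 gives 0.227 and 58%. Reaching 80% needs r of about 0.89 (0.85 one-sided).
- Change from baseline, F = 4(1 − r)/3: r = 0.5 gives 0.667 and 24%; r = 0.8 gives 0.267 and 52%. Reaching 80% needs r of about 0.90 (0.87 one-sided).

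**Precision at 32 per arm.** The 95% half-width is t(0.975) × 1.91 × √F, with t = 2.00.
- Single visit: 3.8
- Mean of three visits, r = 0.5: 3.1
- Baseline-adjusted, r = 0.5: 2.5
- Baseline-adjusted, r = 0.8: 1.8
- Change score, r = 0.8: 1.97
- Mean of all four visits, r = 0: 1.9

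**Evaluable number.** 80 × 0.70 = 56, or 28 per arm. Keeping 64 evaluable needs 64/0.70 = 91.4, so 92. The figure of 80 equals 64/0.80, which is 20% attrition. At 28 per arm, single-visit power is 16% two-sided; baseline-adjusted power is 32% at r = 0.5 and 52% at r = 0.8.

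**The case against.** The best defence is that Table 3 is a repeated-measures calculation whose correlation has been left out of a journal article, and the full protocol or analysis plan may hold it. This has force against any single figure for delivered power. A reader might infer that power is simply 18 to 36%. That range holds only for two-sided alpha, running from a single visit to a baseline-adjusted mean at an assumed r of 0.5. Other admissible assumptions give 43% (three visits, r = 0), 58% (baseline-adjusted, r = 0.8) or 81% (change score, r = 0.9), so the documents do not support that flat range.

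The defence does not rescue the named test, since no undisclosed non-negative correlation brings it to 80%. Reading the ANOVA as an arm-by-time interaction test does not help either. Entering f = 0.131 with four measurements and r = 0.6 gives a total near 64 (N = 66), but a true 2-point post-dose step tested that way has only 19% power at r = 0.6.

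Two further inferences go too far. One is that an observed difference of zero must leave a 95% interval crossing 2 points; the half-widths of 1.8 to 1.97 above show exceptions. The other is that the error arose from entering 2/7.64 = 0.262 as Cohen's f, where the two-group value is 0.131. With three measurements and r = 0.3 this gives N = 64, but that correlation appears nowhere in the article and the interaction entry lands almost as close. The source of 64 cannot be identified, and the point does not depend on it.

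**Conclusion.** The point holds for reproducibility and for the named test. A single comparison needs about seven times the stated number per arm (230/32 = 7.2). The between-factors ANOVA has 18% to 43% power two-sided with three visits, or up to 54% with four; the one-sided maxima are 56% and 67%. The 80% claim is therefore not merely undocumented: the named analysis lacks it. An analysis using baseline could reach 80%, but only at a correlation of about 0.89 (0.85 to 0.87 one-sided). The article neither states nor supports such a value. It would be high for a score expected to fall 7 to 8 points, though the article does not rule it out.

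If 2 points is the margin, an observed difference of zero would not exclude it at low to moderate correlation. The exceptions are high correlation with baseline adjustment or change scores, or averaging all four visits at r = 0. These results assume SD 7.64 at every visit and equal correlation between visits. At Table 3's own attrition rate, 28 rather than 32 per arm would be evaluable and every power figure is lower.

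**What to change.** Correct Table 3:
- State the correlation, number of measurements, sidedness and formula.
- Withdraw the 80% claim for 2 points.
- Restate the power or detectable difference that the planned size delivers, as a range over correlation. For example, for a baseline-adjusted mean of three visits at 32 per arm, two-sided: about 36% at an assumed r of 0.5 and 58% at 0.8.
- Base the final statement on the evaluable number Table 3 implies, 56 in total (28 per arm), or reconcile the attrition rate with the target of 80.

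Adjust the primary analysis for baseline MDAS, which is already collected. At r = 0.5 this lowers F from 0.667 to 0.417, cutting the required number by about 37%.

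The non-inferiority hypothesis stays and no added recruitment is required. The cost is a revised table, one covariate in the primary model, and a less favourable power statement.

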### Recruitment {15}

HCA’s clinical staff attending to the patients under its service will assist in recruitment. As they continue to provide standard palliative care to the patient, the clinical staff will:
(i)Identify patients who meet inclusion criteria and share preliminary information with caregivers,(ii)Confirm the diagnosis of delirium, and(iii)Advise caregivers on appropriate non-pharmacological management.

The clinical staff of the hospice service will be briefed about the study and will refer patients to the research team. The research team will explain the details of the study and collect informed consent from them.

